## Abstract

Prefrailty and sarcopenia in combination are more predictive of mortality than either condition alone. Early detection of these syndromes determines the prognosis of health-related adverse events since both conditions can be reversed through appropriate interventions. Nowadays, there is a lack of cheap, portable, rapid, and easy-to-use tools for detecting prefrailty and sarcopenia in combination. The aim of this study is to validate an iPhone App to detect prefrailty and sarcopenia syndromes in community-dwelling older adults. A diagnostic test accuracy study will include at least 400 participants aged 60 or over without cognitive impairment and physical disability recruited from elderly social centers of Murcia (Spain). Sit-to-stand muscle power measured through a slow-motion video analysis mobile application will be considered as the index test in combination with muscle mass (calf circumference or upper mid-arm circumference). Frailty syndrome (Fried’s Phenotype) and sarcopenia (EWGSOP2) will both be considered as reference standards. Sensibility, specificity, positive and negative predictive values and likelihood ratios will be calculated as well as the area under the curve of the receiver operating characteristic. This mobile application will add the benefit for screening large populations in short time periods within a field-based setting, where space and technology are often constrained (NCT05148351).

## 1. Introduction

Frailty and sarcopenia are syndromes related to the biological ageing process which can lead to adverse health-related consequences. Although not formally recognized as a disease, frailty is defined as a biological state characterized by reduced muscle strength, endurance, and physiological function that increases vulnerability to stressor events including loss of autonomy, disability, falls, hospitalizations, and deaths [1]. Although this syndrome seems to overlap with sarcopenia, in fact they are not synonyms. Indeed, sarcopenia is defined as a generalized and progressive loss of strength, skeletal muscle mass, and physical function [2] and it has been considered a precursor syndrome for developing frailty [3]. However, frailty is a multidimensional geriatric syndrome which not only includes physical but also cognitive and social dimensions. While sarcopenia is now formally recognized as a muscle disease with an ICD-10-MC Diagnosis Code, there is still a need for an ICD code for frailty to promote clinicians, public health agencies, and governments to report diagnosis, treatment strategies, and disease prevalence with enough accuracy [4].

Prevalence studies in European community-dwelling older adults have shown, with regional and criteria-related variations for diagnosis, that approximately 22% of them can be classified as sarcopenic [5], while 17% of them can be classified as frail, with Spain being among the countries with the highest prevalence rates [6]. However, few studies have analyzed the prevalence of both syndromes in combination and have reported prevalence rates of 2.8% and 3.6% in Australian [7] and Japanese [8] community-dwelling older adults, respectively, whereas the prevalence is even higher in the Spanish population, showing rates ranging from 8.2% to 15.7% depending on the diagnostic criteria used [9]. While both syndromes share many common features linked to the ageing process, recent studies have demonstrated that their coexistence increases the incidence of recurrent falls, poor health-related quality of life, and mortality compared to those neither frail nor sarcopenic [7,8]. Although sarcopenia and frailty are not the same condition, their association might respond to the existence of different clinical forms of frailty, i.e., those with or without sarcopenia, with different pathophysiological processes and increased risk of adverse outcomes [7,9,10]. Therefore, assessing sarcopenic status once a patient is diagnosed of frailty would have potential prognostic and diagnostic consequences [9].

Given the growing importance of the early identification of frailty (prefrailty status) and sarcopenia to prevent subsequent functional decline, disability, and the increased mortality risk, a clinical affordable easy-to-use diagnostic tool for detecting prefrailty and sarcopenia syndromes in combination might have implications for prognosis, optimizing care, and planning interventions for community-dwelling older adults. In this regard, time needed to stand from a chair is considered a biomarker of mortality and frailty in older people [1,11], as well as a reliable diagnostic criteria for probable sarcopenia [2]. Although time to complete the sit-to-stand test is the primary measure of function and can be easily measured with a stopwatch, muscle power derived from inertial measurement unit sensors has been associated with frailty and has a greater discriminatory capacity to detect frailty compared to the time to complete the test [12]. Similarly, kinematics data related to muscle power obtained from ground reaction forces have been associated with sarcopenia syndrome and showed an excellent discriminatory ability for detecting sarcopenia in a sample of 627 community-dwelling older adults [13]. However, although this technology seems to be sensitive to detect both syndromes, it is not readily available or affordable in clinical or field-based testing environments and some of the current methods remain complex, difficult and time consuming to analyze.

Recent advances in hand-held technology offer an opportunity to assess muscle power during sit-to-stand test through a smartphone mobile application as valid as a force plate and 3D motion capture cameras [14,15] with the advantage of acquiring muscle power with a short assessment duration and automatic data processing response. Indeed, the purpose of this study is to develop and validate an update of the *Sit-to-Stand* App for detecting prefrailty and sarcopenia syndromes in combination in community-dwelling older adults. Since several studies have shown that low muscle mass measured by calf circumference or mid upper-arm circumference has been associated with frailty and sarcopenia syndromes [16,17], one could expect that the incorporation of these two measures, muscle power and muscle mass, into a single diagnostic tool integrated in a mobile application will result in a portable and unique easy-to-use tool capable of early detecting both syndromes in combination with enough accuracy. This mobile application will add the benefit for screening large populations in short time periods within a field-based setting, where space and technology are often constrained.

## 2. Materials and Methods

### 2.1. Study Design and Protocol Registration

This is a protocol for a retrospective diagnostic accuracy study. Standards for Reporting of Diagnostic Accuracy Studies (STARD) [18] have been used to ensure the completeness and the transparency of this protocol (see Supplementary Materials Table S1). This study has been registered on ClinicalTrial.gov (21/12/08): NCT0514835. This study was approved by the Ethical Committee of Catholic University of Murcia (CE022108) and is in accordance with the principles of the Declaration of Helsinki.

### 2.2. Eligibility Criteria

Participants aged 60 or over will be enrolled at elderly social centers of the city of Murcia (Region of Murcia, Spain). Participants self-reporting severe cardiovascular problems such as heart valve disease, uncontrolled heart rhythm problems, automatic defibrillator, and pacemakers will be excluded. Additionally, participants with a Barthel score less than 90, less than 3 points in the Mini-Cog test, or those who are unable to stand up from a chair without assistance will be excluded from this study. All participants will provide written informed consent to participate in this study.

### 2.3. Participants Recruitment

Centers will be contacted and informed for participation in the development of this study. After obtaining consent from the social centers, each potentially eligible subject will be contacted via telephone or face to face in order to individually provide a detailed explanation of the assessment procedure, as well as to obtain his/her written consent after receiving oral and written information about this study. Participants will be informed that they can withdraw at any time from this study. Participants’ recruitment will be carried out with a convenience model.

### 2.4. General Data Collection

All data collection will be performed at the same day. Data relative to age and sex of the subjects will be collected in form of self-reported questionnaire. Moreover, the following information will be collected through a list of observations: presence of depressive symptoms, socioeconomic status, education level, presence of comorbidity, polypharmacy, number of falls in the last year, number of hospitalizations in the last year and smoking habits. All data will be registered by a single researcher in a spreadsheet and then cross-checked point by point from the original data register by another researcher. Detailed information about general data collection can be found in Table A1.

The procedure for data collection will be performed in the following order: (i) clinical interview; (ii) index test; (iii) frailty assessment; (iv) sarcopenia assessment.

### 2.5. Index Test: Smartphone Mobile Application (App)

Participants’ sit-to-stand capacity will be assessed using an iPhone App called *Sit-to-Stand* (version 1.1.1.) installed on an iPhone 13 device running iOS 15.3; Apple Inc., Cupertino, CA, USA. This App was created to determine muscle power derived from one time rise from a chair using a slow-motion video captured camera (240 frames per second). Participants will sit on a rigid and adjustable height chair with their arms crossed over their chest with their hip, knee and ankle joints visually positioned at 90 degrees. Then, subjects will be instructed to stand from the chair “as fast as possible”, while the execution of the test will be filmed simultaneously with the smartphone. The smartphone will be placed horizontally on a 0.7 m-high tripod placed 3 m from the right or left side of the participant. This App estimates muscle power relative to body weight (in watts per kilogram; W/kg) from the subsequent analysis of the video recording using the following equation:*Muscle Power* = 2.773 − 6.228 × *t* + 18.224 × *d*
where *t* is the time to rising, i.e., the time from seat off until the hip and knee joints reach full extension in an upright stance, and *d* is the femur length of the subject, i.e., the vertical displacement during the sit-to-stand test. Femur length will be measured as the distance between the superior aspect of the greater trochanter and femoral lateral condyle on the participants’ right or left side. A reflective marker will be placed on the greater trochanter in order to identify the start and end of the sit-to-stand movement. The start of the movement is determined when the pelvis began to move forward after anterior trunk tilt which is time-matched when the reflective marker crossed the first horizontal grid line on the screen of the App (Figure 1). The end of the movement is defined when full extension of hip and knee is achieved in an upright stance which is time-matched when the reflective marker achieves the highest vertical point during the upright movement cycle. The results provided from this App has been twice validated against 3D motion capture camera and force plates in community-dwelling older adults [14,15].

In addition, participants’ calf circumference and mid-upper arm circumference will be measured and added together with sit-to-stand power values to improve diagnostic test accuracy. Calf circumference will be measured at the point of greatest circumference on the non-dominant leg (right leg for left-handed persons) in a sitting position with the knee and ankle at 90 degrees. Calf circumference has been shown to predict performance and survival in older people [17]. Mid-upper arm circumference will be measured at the midpoint of the participants’ upper arm between the tip of the acromion and olecranon process of the dominant arm in a sitting position [19]. Both anthropometric measurements will be measured in a relaxed state using an inelastic but flexible measuring tape without compressing the skin.

### 2.6. Reference Standard for Frailty Syndrome

Frailty syndrome will be assessed through frailty phenotype proposed by Linda Fried [20]. Although there is no gold standard for the detection of frailty, this tool is probably the most used in the scientific literature [3]. This multidimensional tool determines frailty through five domains: gait speed, exhaustion, unintentional weight loss, strength and physical activity levels. Gait speed will be assessed using the 4 m gait test at usual and comfortable pace. Unintentional weight loss will be assessed by asking the subject if he/she experienced unintentional weight loss over 4.5 kg through the previous year. Exhaustion assessment will be collected asking to participants to rate from 0 (never) to 3 (most of the time) the frequency with which they experience the following statements: “I felt that everything I did was an effort” and “I could not get going”. Strength level will be assessed using handgrip strength with a Takei 5401 hand grip digital dynamometer (Takei Scientific Instruments Co., Ltd., Tokyo, Japan) and data relative to the physical activity levels of the participants will be collected through the Spanish validated short version of the Minnesota leisure time physical activity questionnaire [21]. The presence of at least 3 of 5 criteria will be necessary to define a frail state, whereas the presence of at least 1 criterion will be sufficient to identify prefrailty state [20].

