### 2.9. Statistical Analysis

The database will be created in Microsoft Excel©, Microsoft Corp., Redmond, WA, USA and the software IBM SPSS Statistics 26.0, SPSS Inc., Chicago, Ill, USA will be used for further analysis. A descriptive analysis of data will be carried out to report the participants’ characteristics. We will provide values represented as mean, standard deviation, and 95% confidence interval (CI) for continuous variables and frequencies and percentages for categorical variables. Kolmogorov–Smirnov’s test will be used to assess the normal data distribution. A data scrub will be performed with range and logic tests and we will search for unknown or unlikely values.

A complete case analysis will be performed. The AUC of the receiver operating characteristic (ROC) will be calculated to identify the best cut-off point of muscle power to discriminate subjects with both syndromes separately and in combination. Then, a multiple logistic regression equation with muscle power and calf circumference or mid upper-limb circumference will be generated and an additional ROC analysis will be performed using predictive probability from the results of the multiple logistic regression analysis to identify the best cut-off point for detecting both syndromes for each sex. Cross-tabulations of the index test with the reference standards (prefrailty and sarcopenia syndromes) will be performed and sensibility, specificity, positive and negative predictive values, and positive and negative likelihood ratios will be calculated. Finally, after classifying the status of the subjects into robust, prefrail, sarcopenia or the combination of both syndromes, the chi-square tests will be used to assess differences in proportion regarding their clinical profile (Table A1) and the Odds Ratio with 95% CI will be calculated.

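### Prefrailty has no upper limit and frail participants have no place in the analysis, so the accuracy target is either any frailty criterion or undefined

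*Protocol article*

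**What the plan says.** Section 2.6 gives two thresholds on the same five-item count. For frailty: "The presence of at least 3 of 5 criteria will be necessary to define a frail state". For prefrailty: "the presence of at least 1 criterion will be sufficient to identify prefrailty state". No upper limit is attached to the second.

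Section 2.9 uses the count in two places. For the accuracy tables: "Cross-tabulations of the index test with the reference standards (prefrailty and sarcopenia syndromes) will be performed". For the closing comparison of clinical profiles, the chi-square tests and odds ratios come "after classifying the status of the subjects into robust, prefrail, sarcopenia or the combination of both syndromes". Frail is named in neither.

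Section 2.2 excludes people with severe cardiovascular problems, those who cannot rise unaided, and "participants with a Barthel score less than 90, less than 3 points in the Mini-Cog test". Frailty itself is not an exclusion.

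The Introduction places the interest at the early stage: "Given the growing importance of the early identification of frailty (prefrailty status) and sarcopenia". The Discussion repeats this, and the Conclusions link early detection to reversibility.

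**The concern.** A person with four criteria satisfies both definitions in section 2.6, is eligible under section 2.2, and has no category of their own in section 2.9. The protocol therefore does not fix who counts as a case for its frailty-related target, either alone or combined with sarcopenia.

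This matters because the App's cut-off is to be read off the ROC curve and offered as a tool for early detection. People with three or more criteria can be expected to have lower sit-to-stand power: gait speed and grip strength are two of the five criteria, and the Introduction cites an association of muscle power with frailty. If they sit among the cases, sensitivity and AUC will probably look better than they are for people with one or two criteria, and the cut-off may move toward frail performance. If they sit among the controls, specificity probably falls. If they are dropped, the evaluable sample shrinks. Two analysts with the same data could build different two-by-two tables.

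**Working it through.** **Step 1: place each criteria count under the two readings of section 2.6.**

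| Criteria met | Literal reading | Hierarchical reading (3 or more overrides) |
|---|---|---|
| 0 | robust | robust |
| 1–2 | prefrail | prefrail |
| 3–5 | frail and also prefrail | frail only; no category in section 2.9 |

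The literal reading turns the prefrail target into any frailty criterion. The hierarchical reading leaves the last row unassigned in the accuracy tables and in the final grouping. Neither yields a complete classification in which prefrail means the early stage.

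**Step 2: how many people are affected.** The Introduction says of European community-dwelling older adults that "17% of them can be classified as frail". Applied to the planned 200 per sex, 0.17 × 200 = 34 people per sex. The enrolled number is probably smaller, for the reasons given under the objection.

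**Step 3: frail share among combined cases.** For frailty with sarcopenia in Spain, the Introduction reports studies "showing rates ranging from 8.2% to 15.7% depending on the diagnostic criteria used". For prefrailty with sarcopenia, section 2.8 gives 13% to 40%. If the two groups are disjoint, the share is f = F / (F + P), with F the frail-sarcopenic and P the prefrail-sarcopenic prevalence:

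| F | P | f |
|---|---|---|
| 8.2% | 40% | 8.2 / 48.2 = 17% |
| 15.7% | 40% | 15.7 / 55.7 = 28% |
| 8.2% | 13% | 8.2 / 21.2 = 39% |
| 15.7% | 13% | 15.7 / 28.7 = 55% |

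If the 13–40% range instead already contains frail people, f = F / P. The four pairings then run from 8.2 / 40 = 21% to 15.7 / 13 = 121%. The last is impossible, which shows that the two ranges cannot be freely combined. The 17% to 55% is an order of magnitude only. No such share can be formed for prefrailty alone, because the article gives no prevalence for it.

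**Step 4: what pooling does, under assumed accuracies.** With the control group held fixed,

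AUC(pooled) = (1 − f) × AUC(prefrail) + f × AUC(frail),

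so the rise over the prefrail value is f × [AUC(frail) − AUC(prefrail)]. The same identity holds for sensitivity at a fixed cut-off. The documents give no accuracy by stage. Assume AUC 0.65–0.75 for 1–2 criteria and 0.85–0.95 for 3–5, a difference of 0.10 to 0.30:

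- f = 0.20: rise of 0.02 to 0.06
- f = 0.40: rise of 0.04 to 0.12

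For example, with 0.70 and 0.90 the pooled AUC is 0.74 at f = 0.20, 0.78 at f = 0.40 and 0.80 at f = 0.50. The last equals the AUC in section 2.8 although the prefrail value is 0.70. These figures show the mechanism and are not estimates.

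**Step 5: cases left after separating the strata.** At 13% prevalence, 0.13 × 200 = 26 combined cases per sex. If that 13% includes frail people, which the article does not say, restricting to 1–2 criteria leaves 26 × (1 − f): about 23, 21, 18 and 16 at assumed f of 0.1, 0.2, 0.3 and 0.4.

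**The case against.** The strongest reply is that pooling is one reading, not a stated fact. Section 2.6 names a separate frail state, contrasts it with the prefrail threshold in the same sentence, and takes both from a published phenotype. A reader may reasonably take 3 or more as overriding. That stands, and it means inflated sensitivity and AUC cannot be asserted as a certain consequence. It does not clear the plan, because frail participants then have no defined place.

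Second, a reader might infer that the four-group classification is the ROC target. It is not. It belongs to the final chi-square and odds-ratio step. The evidence for the accuracy analysis is the cross-tabulation sentence, which names prefrailty and sarcopenia only.

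Third, any numerical bias is fragile. The prevalences come from different sources and criteria. The Barthel and chair-rise exclusions, and the fitter social-centre sample acknowledged in the Discussion, probably lower the frail share, though they do not make it zero. This stands in full.

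Fourth, a target of prefrail or worse is legitimate for a screening tool. That is true if it is so named; the fault lies in reporting it as prefrailty.

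Finally, this is a condensed article, and detail may sit in a fuller document. But the point does not rest on an omitted detail: the definition is stated here, and as stated it overlaps with frailty.

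**Conclusion.** The concern holds in this form: the prefrail definition overlaps the frail one, frail people are eligible, and the analysis assigns them no category. On the literal reading, the accuracy reported for prefrailty is accuracy for any frailty criterion, probably optimistic for the early stage. On the hierarchical reading, their status as cases, controls or exclusions is undefined.

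A reader might go further and conclude that the published sensitivity will be overstated by a known amount. The documents do not support that. The frail share of 17% to 55% assumes disjoint groups and mixes sources, and the AUC shifts in step 4 rest wholly on assumed values. The shift in cut-off is plausible but has not been quantified.

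This should be fixed before analysis. No stated figure is shown to be wrong, and the criteria count is collected for everyone, so the defect is fully repairable.

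**What to change.** 1. In section 2.6, define prefrail for the analysis as 1–2 criteria and frail as 3–5.
2. In section 2.9, name the target of the ROC analyses and cross-tabulations. Either use prefrail or frail (1 or more criteria), with sensitivity also reported separately for 1–2 and 3–5 criteria; or use 1–2 versus 0 criteria, with frail participants shown separately. Apply the same choice to the target combined with sarcopenia.
3. Add frail, with and without sarcopenia, to the final classification used for the chi-square tests and odds ratios.

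The cost is wording and one further breakdown of data already collected. The downside is that estimates in the 1–2 group rest on fewer cases, so they will be less precise and probably less favourable.
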